### 2.5. Physical Activity

Physical activity will be monitored using the short version of the International Physical Activity Questionnaire (IPAQ-SF) [46]. IPA-SF quantifies physical activity during the previous seven days and is divided into four categories: vigorous intensity, moderate intensity, walking and sedentary behaviour. Furthermore, intensity, frequency and duration of physical activity are also assessed. Data obtained from the IPAQ-SF will be used to estimate the total amount of physical activity completed in a seven-day period by weighting the reported minutes per week in each of the four physical activity categories by a metabolic equivalent (MET) energy expenditure estimate. MET minutes per week will then be calculated by multiplying the duration (minutes), frequency (days) and MET intensity, and summing across the different categories of physical activity (vigorous, moderate, walking and sedentary behaviour). Participants will be asked to maintain their usual levels of physical activity throughout the intervention period. Physical activity levels will be collected at baseline and week 12.

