### 2.9. Dietary Protocol

Participants will be randomly allocated to either a 12 week prescribed and individualized ad libitum MedDiet intervention; or a 12 week prescribed and individualized ad libitum healthy eating (HE) dietary approach. Participants randomized to the HE dietary approach will be asked to follow a dietary pattern consistent with the Australian Dietary Guidelines and Australian Guide to Healthy Eating. Specifically, this will include a dietary pattern consisting of wholegrain breads and cereals, vegetables, fruit, low-fat dairy, lean meat, poultry and fish and small servings of unsaturated fats.

The MedDiet intervention will be in line with traditional MedDiet principles yet adapted to suit the dietary and cultural preferences of the Australian population. Notably, the MedDiet intervention will emphasize a high intake and wide variety of plant-based foods (fruits, vegetables, wholegrains, legumes and nuts), liberal and exclusive use of extra virgin olive oil (EVOO), moderate intake of fish and seafood and red wine with a limited or null intake of processed foods, butter and red or processed meat. The specific details for each of the dietary approaches, including target serving sizes, are outlined in Table 2. Nil caloric restriction will be prescribed for either dietary approach, and participants will be asked to maintain their habitual physical activity levels throughout the study duration.

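### The physical activity total adds MET-weighted sedentary time to active time, so the score can mask or reverse a real change in activity

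*Protocol article*

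**What the plan says.** Section 2.5 (Physical Activity) describes the IPAQ-SF as "divided into four categories: vigorous intensity, moderate intensity, walking and sedentary behaviour". The data are to be "used to estimate the total amount of physical activity completed in a seven-day period". Two scoring steps follow. The first is "weighting the reported minutes per week in each of the four physical activity categories by a metabolic equivalent (MET) energy expenditure estimate". The second multiplies duration, frequency and MET intensity, and forms the total by "summing across the different categories of physical activity (vigorous, moderate, walking and sedentary behaviour".

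The same section adds: "Participants will be asked to maintain their usual levels of physical activity throughout the intervention period". Section 2.9 (Dietary Protocol) repeats the request for both diets: "participants will be asked to maintain their habitual physical activity levels throughout the study duration". On timing, section 2.5 says: "Physical activity levels will be collected at baseline and week 12".

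The article gives no MET value for any category. It does not give sedentary time a zero or negative weight, and it does not say that sitting will be reported apart from the total.

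**The concern.** The score is meant to measure how much physical activity was done. Sedentary behaviour is the absence of activity, yet it enters the total with the same sign as the active categories. It is named as a category and listed again in the summation, so this does not read as a slip in one sentence. A woman who does the same exercise but sits longer gets a higher activity score. A woman who becomes less active may show little change, or even an increase.

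What is at stake is interpretation. Women in both arms are asked to hold activity steady so that a difference between the arms can be attributed to diet, and this score is the only activity measure the article describes. If it hides a change, readers cannot tell from it whether activity stayed stable or drifted apart between the arms. Section 3 (Analyses of Results) also adjusts for potential covariates without naming them. If activity were among them, the adjustment would use a variable that consists largely of sitting time under plausible inputs.

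**Working it through.** The article states no value of the score, so there is no figure of its own to reproduce. The check applies its rule directly.

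**Rule.** Let A be the MET-minutes per week from vigorous, moderate and walking activity, M the sedentary minutes per week, and w the MET weight for sedentary time. Section 2.5 gives

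S = A + w × M, so ΔS = ΔA + w × ΔM.

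For any w > 0, S rises with M when A is unchanged. The sign does not depend on the value of w. When activity falls, S still rises if w × ΔM is larger than the loss in A.

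**Example 1.** All inputs are assumptions: weights of 4.0 (moderate), 3.3 (walking) and 1.0 (sitting); 150 min/week moderate, 150 min/week walking, no vigorous activity; 8 h/day sitting.

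- A = 150 × 4.0 + 150 × 3.3 = 600 + 495 = 1,095
- w × M = 8 × 60 × 7 × 1.0 = 3,360
- S = 1,095 + 3,360 = 4,455; sitting share = 3,360 / 4,455 = 75%

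Now halve the activity, so that A = 547.5 and 150 active minutes per week are lost.

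| Change in sitting | w × M | S | Change in S | Change in A |
|---|---|---|---|---|
| The 150 lost minutes become sitting | 3,510 | 4,057.5 | −397.5 (−9%) | −50% |
| Sitting rises by 2 h/day | 4,200 | 4,747.5 | +292.5 (+7%) | −50% |

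The score stays level when extra sitting reaches 547.5 / 7 = 78 min/day. Below that the fall is understated; above it the direction reverses.

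**Example 2: range over the unknown sedentary weight.** Assumed baseline: 60 vigorous, 90 moderate and 150 walking min/week (weights 8, 4 and 3.3) and 6 h/day sitting. Then A = 480 + 360 + 495 = 1,335 and M = 2,520. Assumed week 12: 30 min/week less in each active category, so A = 240 + 240 + 396 = 876, a fall of 459 (34%).

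| w | S at baseline | Sitting share | ΔS, 90 lost min become sitting | ΔS, sitting up 2 h/day | Extra sitting that hides the fall |
|---|---|---|---|---|---|
| 1.0 | 3,855 | 65% | −369 | +381 | 66 min/day |
| 1.3 | 4,611 | 71% | −342 | +633 | 50 min/day |
| 1.5 | 5,115 | 74% | −324 | +801 | 44 min/day |

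With activity unchanged, 2 h/day more sitting adds 840 × w, that is 840 to 1,260 MET-min/week.

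**After the correction.** Without the sedentary term, example 2 goes from 1,335 to 876 (−459), and extra sitting with unchanged activity moves the total by 0.

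**The case against.** The strongest reply is that the score has no stated analytic role. Physical activity is not among the primary or secondary outcomes in section 2.2 (Data Collection), section 3 names no covariates, and no test, threshold or decision uses the score. The article is also condensed, and it cites a source for the instrument that is not at hand. Minutes are reported by category, so an active-only total can be recomputed at any time. The 7% rise in example 1 needs 840 extra sitting minutes per week against 150 active minutes lost; a plain swap leaves the direction right.

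Much of this stands, and it rules out several stronger readings that a reader might infer.

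- *A formal check of unchanged activity gives the wrong answer.* The article describes no such check, only a request to maintain activity and two measurements.
- *Adjusting for the score would push the diet effect the wrong way.* ANCOVA estimates the covariate's coefficient, including its sign, from the data. A badly scored covariate adjusts less well; it does not by itself reverse the adjustment.
- *Sitting dominates the total for any positive weight.* In example 1 it exceeds half only when w is above 1,095 / 3,360 = 0.33. Even at w = 1.0, adding 300 min/week of vigorous activity at an assumed 8 METs (2,400) gives 3,495 active against 3,360 sitting.
- *The score always reverses.* It does so only when added sedentary MET-minutes exceed the active MET-minutes lost.

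The reply does not remove the core point. The article does not leave the formula to another document: it states one, and that formula does not measure what the article says it measures. Reversal is not needed for harm either, since a halving of activity that shows as a 9% fall would pass for near stability.

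**Conclusion.** The point holds as a scoring error. As written, the physical activity total rises with sedentary time for any positive sedentary weight, so it can mask or reverse a real change. The direction of that effect follows from the stated rule alone. The size rests on assumed weights and minutes: sitting makes up 65% to 75% of the baseline totals worked here, and roughly 45 to 80 min/day of extra sitting hides falls in activity of 34% to 50%.

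The consequence is limited. The only activity measure described could mislead on whether activity stayed stable or differed between the diets, and it would be a poor covariate if chosen. Nothing in the article supports the inference that the primary HOMA-IR comparison is itself invalid, because the score does not enter that comparison as described.

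**What to change.** In section 2.5, define total physical activity as the sum of MET-minutes per week over vigorous, moderate and walking activity only. State the MET weight used for each. Report sedentary time separately, in minutes per day. Present both measures by diet group at baseline and week 12. If activity is to be a covariate, use the active-only total.

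If sedentary time was never meant to enter the total, correcting the two sentences is enough.

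The cost is negligible. The same questionnaire supplies both quantities, no further data are needed, and any data already collected can be rescored from the category minutes.

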### 2.6. Dietary Intake

Dietary intake will be recorded using a 4 day food record at baseline, week 6 and week 12 of the study. Prior to each of these assessments, participants will be provided with a 4 day food record and set of written instructions by the study dietitian on how to complete their record. Participants will be asked to record all food and beverage intake for a period of 4 days (3 weekdays and 1 weekend day) using standard household utensils such as standard cup, teaspoon and tablespoon measures, before returning the food record back to the study dietitian at the next appointment. Once returned, all food records will be verbally cross-checked for completeness by the study dietitian, and any ambiguities will be clarified with the participant. All food records (baseline, week 6 and week 12) will be entered into Foodworks, version 10 (Xyris Ltd., Brisbane, Australia) by the study dietitian for a comprehensive nutrient analysis assessment using the Australian Food Composition database. Participants will also be provided with detailed instructions on how to maintain and record their daily dietary checklist. If any deviations are made from the prescribed quantities in the checklist, participants will be instructed to record this. Participants will be instructed to return the dietary checklists each fortnight for the duration of the study and will be used as an additional measure of compliance toward the dietary protocol.

### 2.7. Adherence to the MedDiet Intervention

Adherence to a MedDiet will be assessed at baseline and week 12 using the previously validated 14-item MEDAS, used in the Prevención con Dieta Mediterránea (PREDIMED) study [47]. The MEDAS assesses adherence to a MedDiet according to pre-defined normative criterion cut-offs for the habitual frequency of consumption (pre-defined servings/day or servings/week) of 12 main dietary elements and two food habits related to a traditional MedDiet pattern. Each item in the questionnaire is dichotomously scored as either 0 or 1, producing a maximum score of 14. Greater adherence to a MedDiet is indicated by a higher score. Specifically, a MEDAS score ≥10 is suggestive of high adherence, scores between 6 and 9 indicate moderate adherence, and a score ≤5 is considered low adherence. Participants will complete the MEDAS at study screening for assessment of eligibility and again at 12 weeks.

### 2.8. Demographic Questionnarie

At baseline only, participants will be asked to complete a series of sociodemographic questions related to age, country of birth, cultural background, level of mobility, smoking status, education, socioeconomic status, current medical conditions, medication and supplement use.

### 2.9. Dietary Protocol

Participants will be randomly allocated to either a 12 week prescribed and individualized ad libitum MedDiet intervention; or a 12 week prescribed and individualized ad libitum healthy eating (HE) dietary approach. Participants randomized to the HE dietary approach will be asked to follow a dietary pattern consistent with the Australian Dietary Guidelines and Australian Guide to Healthy Eating. Specifically, this will include a dietary pattern consisting of wholegrain breads and cereals, vegetables, fruit, low-fat dairy, lean meat, poultry and fish and small servings of unsaturated fats.

The MedDiet intervention will be in line with traditional MedDiet principles yet adapted to suit the dietary and cultural preferences of the Australian population. Notably, the MedDiet intervention will emphasize a high intake and wide variety of plant-based foods (fruits, vegetables, wholegrains, legumes and nuts), liberal and exclusive use of extra virgin olive oil (EVOO), moderate intake of fish and seafood and red wine with a limited or null intake of processed foods, butter and red or processed meat. The specific details for each of the dietary approaches, including target serving sizes, are outlined in Table 2. Nil caloric restriction will be prescribed for either dietary approach, and participants will be asked to maintain their habitual physical activity levels throughout the study duration.

### 2.10. Education and Counselling

All participants will receive individual dietary counselling and education by the study dietitian each fortnight for the duration of the study (5 sessions in total, 30 min in duration each). Both dietary protocols will be presented to participants in the form of a dietary checklist outlining key foods and recommended target serve sizes (daily/weekly) for participants to achieve. Dietary checklists will also be discussed with the study dietitian to clarify serving sizes and address any potential issues or problems with compliance toward the dietary protocol. To further facilitate dietary compliance, all participants (irrespective of their group allocation) will be provided with a suite of written educational resources presented in the form of an information pack developed by the research team. Specifically, the information pack will include a fridge magnet, shopping lists, meal suggestions, recipes, label reading resources, health pamphlet and a pictorial display of the recommended number of serves and serve sizes for all recommended foods. In addition, all participants will receive weekly one-way text messages designed to facilitate behaviour change and provide a health prompt to facilitate dietary compliance.

The provision of education and counselling for all participants will further involve mutually set Specific, Measurable, Achievable, Realistic, Timely (SMART) goal principles and established action plans for achieving these goals. The SMART goals will be individualized and adapted to the capacities of women so that the counselling and the SMART goals are tailored to the health literacy levels of women. Participants will further be asked to assess their level of confidence in executing their goals, how important they feel the goal is for adhering to the dietary intervention and provide self-reported feedback of goal implementation. In addition to the provision of counselling and education toward the dietary protocols, each of the fortnightly study visits will be structured around central themes related to each of the dietary protocols. Specifically, this will include exploring cooking skills and availability of cooking equipment, convenience meals and options for eating out (week 2) and building skills around goal setting, problem-solving and self-efficacy (week 4). The following consultations will provide education on the specific components of each of the dietary protocols, including dietary fats and label reading (week 6), fruit and vegetable intake (week 8), and intake of wholegrain breads and cereals (week 10). Further, we developed an advisory committee consisting of an Obstetrician and Gynecologist, Endocrinologist, Dietitian and a consumer representative who provided additional strategic advice related to the development of the study protocol, and the development and presentation of educational resources to ensure maximum engagement with the target population.

### 2.11. Digital Messaging

To further promote study engagement and facilitate dietary compliance, all participants, independent of their group allocation, will receive health prompts in the form of weekly one-way text messages. Text message support has been shown to be an acceptable and positive approach to facilitate adherence to multiple lifestyle behaviour changes in patients with coronary heart disease [48]. Moreover, such techniques have been identified as beneficial to promote adherence to healthy eating principles [49], including adherence to a MedDiet [50] and to improve diet quality in adults with T2DM [51] and CVD [52]. Nevertheless, it has previously been identified that text message support is more suitable as an ‘add-on’ to a behavioural and lifestyle intervention led by medical professionals [53]. Text messages will be standardized for each dietary protocol such that each participant will receive the same text messages as other participants in their treatment allocation. Moreover, the messages have been developed to align and address components of the COM-B model [54].

### 2.12. Acceptability and Feasibility of the MedDiet Intervention: Theoretical Frameworks into Practice

Understanding the relationship between behaviour change techniques (BCTs) and mechanisms of action (i.e., the processes through which BCTs influence behaviour), helps inform the development of behaviour change interventions [55,56,57]. Specifically, in the context of the present study, using behavioural theory to identify the determinants of behaviour change can increase the likelihood of the intervention being effective [58]. The Capability, Opportunity, Motivation (COM-B) model of behaviour [56] in combination with the BCT Taxonomy [59] will be employed in the development and evaluation of the MedDiet intervention (Table 3). Specifically, the 93-item hierarchical BCTs have been developed as a method for specifying, evaluating, and implementing behavioural change interventions [59]. In the proposed study intervention, we have utilized specific BCT to help encourage self-management as they are important components to lifestyle interventions to help individuals initiate [60] and sustain the healthy lifestyle behaviours [61]. Further BCTs were also included to facilitate dietary behaviour change and address barriers for dietary adherence [62,63,64]. The COM-B model suggests that for any behaviour to occur, a person must possess the psychological and physical capability to perform the intended behaviour; the physical and social opportunity to engage in the behaviour and must be motivated to do so. In order to capture important distinctions, these three components are further divided into two subcategories (Figure 2). ‘Capability’ is subdivided into psychological capability and physical capability, ‘opportunity’ is subdivided into physical opportunity and social opportunity and ‘motivation’ is subdivided into reflective processes and automatic processes. Importantly, the use of the COM-B model for the development of behaviour change interventions comprises a systematic, theory-based approach that is aligned with the Medical Research Council recommendations when developing an intervention [65]. Furthermore, the COM-B model has also been used for the identification of barriers and enablers related to adherence toward lifestyle modification interventions, such as diet and physical activity, including women with PCOS [66,67,68].

### 2.13. Participant Interveiws

Participants randomized to receive the MedDiet intervention will also participate in a face-to-face individual semi-structured interview with an Accredited Practicing Dietitian (NS) who has previous qualitative experience and training, at the completion of the baseline and week 12 assessments. Interviews will be audio-recorded, and any noteworthy context or ideas identified by the researcher will be annotated in the individual participant record at the end of the assessment. No other researchers will be present during the time of the interviews. Each interview will consist of six opened-ended questions related to capability, opportunity, motivation and behaviour (COM-B) toward adopting a MedDiet and is expected to take approximately 30–45 min to complete (Table 4). Moreover, the same study participants will be asked a series of questions answered using a Likert scale, to assess their level of confidence in their ability to adhere to a MedDiet (Table 5). Specifically, participants will be asked to rate themselves in relation to eight explicit statements. Scores range from one, indicating very high, to five, indicating very low or no confidence. Upon completion of the study (week 12 assessment), participants will be asked to repeat the exercise, providing a rating of their level of confidence in their ability to adhere to a MedDiet compared with their feelings when assessed at baseline. The design of the semi-structured interview questions and the Likert scales were guided by the COM-B framework [54] (See Table 4 and Table 5).

Furthermore, at the week 12 assessment, we will also assess the feasibility of the MedDiet intervention, where participants will be asked a further six open-ended questions to assess participants’ attitudes and opinions on the educational resources provided throughout the intervention, suggested improvements, and their feelings towards following a MedDiet, independent of caloric restriction and/or weight loss (Table 6). Moreover, participants will also be asked a series of Likert scale questions to indicate their level of agreement to 18 explicit statements regarding the provision of the educational resources and the program delivery (Table 7). Specifically, participants will be asked to indicate their agreement with 18 statements, with a score ranging from one indicating a strong agreement to five indicating strong disagreement. The open-ended questions and Likert scales have been developed based on the feasibility framework published by Bowen et al. [70]. As such, the framework proposes that there are eight general areas of focus addressed by feasibility studies—acceptability, demand, implementation, practicality, adaptation, integration, expansion and limited-efficacy testing [70].

